### Randomization, blinding and treatment allocation

2.10

Subjects will be assigned to one of the three study groups using a computer generated randomization list. The recruitment of the patients will be performed by one investigator. All the measurements at the baseline and follow ups will be performed by the second investigator. Patient, the operator (until the gel will be handed over by the dental assistant), the investigator who is taking the measurement and the statistician will be blinded about the intervention groups. This will be ensured by giving codes to the intervention groups only known to the principal investigator who is not involved in the measurement and interaction with the patient.

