## Introduction

1

Gingivitis is one of the most prevalent diseases that affects 82% of adult population in the United States [1]. Dental plaque has been established as an etiological factor in the development of gingivitis and periodontitis [2]. Plaque is primarily composed of bacteria in a matrix of salivary glycoprotein and extracellular matrix and removal of this bacterial biofilm is the cornerstone in the treatment of gingivitis and periodontitis [3]. Bacterial biofilm is primarily disrupted mechanically by scaling and root planning, however, several studies have shown that mechanical debridement alone sometimes remains insufficient in the removal of flora responsible for the periodontal diseases [4], [5]. Due to this reason chemical plaque removal agents as an adjuvant to mechanical therapy have gained popularity [6], [7], [8].

The ultimate goal is to remove the offending pathogens; therefore, several approaches have been employed to treat gingivitis based on the systemic and topical administration of antimicrobial agents [9], [10]. Since, the prolonged use of systemic antimicrobials can lead to increased antibiotic resistance, nausea and diarrhea; therefore, investigators are now focusing on the development of localized drug delivery systems that can allow maximum concentration on the target site, thus minimizing the potential systemic effects [11], [12].

Several antimicrobials including Chlorhexidine and Metronidazole have been used as an adjuvant to mechanical plaque removal. Chlorhexidine is the gold standard mouthrinse to treat gingivitis. Several studies have proved that adjuvant use of Chlorhexidine does not provide additional benefits on periodontitis. It has s broad antiseptic spectrum and substantivity [13]. It acts by directly altering the integrity of bacterial cell membrane [10], [14], [15]. However, its use is discouraged because of its unpleasant taste and undesirable tooth staining [13].

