### Study design

2.3

Triple blind randomized clinical trial.

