### Procedure

2.9

On the first visit after clinical examination, the specially designed baseline study proforma will be filled-in. The bleeding sites, probing depth and the gingival index score will be calculated for all the teeth (six sites per tooth).

Group A subjects will be instructed to apply a standard 0.2 % Chlorhexidine gel (clinica gel) on the marginal gingiva for the next 14 days, twice a day for 3 minutes, after morning and evening tooth brushing.

Group B subjects will be instructed to apply 0.8 % Metronidazole gel (anaerobic gel) twice daily for 2 minutes for two weeks.

Group C subjects will be instructed to apply 0.2% Chlorhexidine gel (clinica gel) on the marginal gingiva after morning tooth brushing and 0.8% Metronidazole gel (anaerobic gel) after evening tooth brushing. Subjects in these groups will receive the detailed and precise instruction and demonstrations on the diurnal alternate application of the two gels.

The application of the topical gels will be halted after 2 weeks and second clinical examination will be carried out for bleeding sites, probing depth and the gingival index score for all the teeth (six sites per tooth). Scaling & polishing of teeth in all three groups and oral hygiene instructions will be reinforced. Subjects will be recalled at 6 weeks for evaluation of gingival and oral hygiene indices. The reading will be recorded in the study proforma.

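### The trial is labelled triple blind and relies on group codes, but codes cannot blind Group C patients, who alternate two different gels while Groups A and B use one

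*Protocol article*

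**What the plan says.** Study design (2.3) consists of one statement: "Triple blind randomized clinical trial".

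Randomization, blinding and treatment allocation (2.10) names the blinded parties as "Patient, the operator (until the gel will be handed over by the dental assistant), the investigator who is taking the measurement", and adds "and the statistician will be blinded about the intervention groups". It then gives the means: "This will be ensured by giving codes to the intervention groups only known to the principal investigator". That section also separates recruitment from measurement, assigning them to two different investigators.

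Procedure (2.9) sets out the regimens:

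- Group A: chlorhexidine gel, "twice a day for 3 minutes, after morning and evening tooth brushing".
- Group B: metronidazole gel, "twice daily for 2 minutes for two weeks".
- Group C: chlorhexidine gel after the morning brushing and metronidazole gel after the evening brushing, with no application time stated. The same paragraph promises "detailed and precise instruction and demonstrations on the diurnal alternate application of the two gels".

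**The concern.** Blinding of patients is a stated property of the design, and the document says how it is secured. The regimens in the neighbouring section have a feature that this means cannot conceal: one arm uses two products and the others use one.

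This matters because the gels are self-applied for 14 days alongside home oral hygiene, and the primary outcome is bleeding on probing at two and six weeks. Patients who know they have the two-gel regimen may clean more carefully, or may mention it to the examiner. Either could shift the bleeding score in comparisons involving Group C. The sample size (2.5) is built on metronidazole against the combination, which is such a comparison. Readers who take the label at face value would also give the result more credit for protection against bias than the design earns.

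**Working it through.** The point turns on whether the stated means can produce the stated blinding. The only arithmetic is the number of patients affected.

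**Number affected.** Sample size (2.5) plans 30 patients in each of three groups: 3 × 30 = 90, as stated. Group C is 30 of 90, or one third. Of the three pairwise comparisons (A v B, A v C, B v C), two involve Group C.

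**Each party in 2.10 against 2.9:**

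| Party | What 2.10 claims | What 2.9 describes | Can group codes deliver it? |
|---|---|---|---|
| Patient, Group C | Blinded | Applies one gel in the morning and another in the evening | No. The patient carries out the alternation |
| Patient, Groups A and B | Blinded | One gel each; 3 minutes in A, 2 minutes in B | Possibly. Each patient sees only his or her own regimen |
| Operator | Blinded until the gel is handed over | Not named in 2.9 | Up to handover only, and nothing beyond that is claimed |
| Measuring investigator | Blinded | Examines at baseline and follow-up | Yes, unless the patient discloses the regimen |
| Statistician | Blinded | Not involved in treatment | Yes |

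**Group C.** To follow the regimen, the patient must be told to use two gels and when to use each. That knowledge comes from the instruction itself, so no coding of groups removes it. It would identify the arm to any patient who knows that only one arm uses two gels. Data collection procedure (2.7) promises patients detailed study information before consent but does not say how far it describes the arms. Even without that knowledge, the patient is not blind to the regimen.

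**Groups A and B.** The different times unmask a patient only if he or she knows the other arm's time, and the article does not say that this is disclosed. The Introduction says of chlorhexidine that "its use is discouraged because of its unpleasant taste and undesirable tooth staining". This is general background, placed after a sentence on chlorhexidine as a mouthrinse, and does not describe a 0.2% gel used for 14 days. Staining could not separate A from C in any case, since both use chlorhexidine.

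**What remains.** Examiner and statistician blinding can be supported by codes. Patient blinding fails for Group C and is undetermined for A against B. Operator blinding ends at dispensing, which is closer to allocation concealment than to blinding during treatment.

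**The case against.** The strongest reply is that a journal article condenses the full protocol, which may describe over-labelled tubes or other masking. That is fair for packaging. Naming the brands does not show that commercial tubes are handed out, so nothing is concluded from their use. Plain packaging alone, however, does not hide that Group C uses two gels where A and B use one. The conflict is between statements the article does make.

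Several stronger readings are tempting, and the document does not support them:

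- *Operator blinding is claimed and not delivered.* It is claimed only up to handover. Nor does Procedure say that the operator does the scaling, which is listed after the week-2 examination and so would not affect that reading.
- *Groups A and B can tell themselves apart.* This is possible through time, taste or staining, but not shown.
- *Only Group C receives demonstrations.* The sentence speaks of these groups in the plural, so who receives them is unclear. Alternation itself, though, belongs only to Group C.
- *One disclosure would unmask all 30 patients in an arm.* That depends on how codes are placed on tubes and records, which is not described.
- *The 3- and 2-minute times confound A against B.* Different times for different products are not in themselves a contradiction, and the choice of time is a clinical matter.

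It also stands that all three arms are active and that a separately blinded examiner is an important safeguard for an examiner-scored outcome. This limits the likely harm but does not make Group C patients blind.

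**Conclusion.** The point holds for patients in Group C: 30 of 90, on the planned equal allocation. As described, group codes cannot blind them to their regimen, so the triple-blind label and the statement that codes ensure patient blinding are wrong as written. The operator should not count towards the label, because the plan itself ends that blinding at dispensing.

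A reader might infer that the trial is effectively open label. The document does not support that: examiner and statistician blinding remain achievable, and failure between A and B is not established. The size of any bias cannot be estimated from the document.

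The conclusion assumes that Group C patients are told they have two gels, as Procedure indicates, and that no dummy or common two-tube scheme exists in the full protocol. If such a scheme exists, the article should state it. The trial remains analysable; the correction is to the blinding claim and, for patients still to be enrolled, to how the gels are presented.

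**What to change.** Reconcile Study design (2.3), Procedure (2.9) and Randomization, blinding and treatment allocation (2.10) in one of two ways.

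1. **Mask the regimen.** Supply every patient with two plain, patient-numbered tubes marked morning and evening: both chlorhexidine in A, both metronidazole in B, one of each in C. Use the same form of instruction and demonstration for all. The gels in each arm are unchanged. Group B's schedule is given only as twice daily, so the investigators should check that the tube labels agree with it. This hides the number of products but not a difference in taste or appearance between a Group C patient's two tubes, so patient blinding should still be described with that limit.
2. **Restate the design.** Where masking is not possible, and for patients already enrolled (Trial status says recruitment has started), describe the trial as examiner- and statistician-blind, with patients not blinded.

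Under either option:

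- Ask patients not to discuss their gel with the examiner.
- Describe the operator as unaware of allocation until dispensing, and leave the operator out of the blinding label.
- Reconcile the application times (3 minutes in A, 2 minutes in B, none stated in C) with the blinding claim. Which time applies is for the investigators to decide.

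The cost is minor repackaging and labelling under the first option, or a less favourable blinding label under the second. Neither changes the sample size.

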## Data analysis

3

Data will be analyzed using SPSS version 20. Descriptive statistics for variables such as age, baseline clinical parameters including probing depth, bleeding sites, gingival index, and oral hygiene index will be computed. An intention to treat analysis approach will be adopted. Generalized estimation equation (GEE) will be run to account for the correlated data (six probing sites per tooth) for the comparison of study arms. Friedman test will be used to assess the bleeding sites among three study groups at the baseline and endpoint. Similarly, gingival index and oral hygiene index in the three groups at baseline, after 2 weeks and 6 weeks will be compared. The level of significance will be kept at 0.05.

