### Sample size

2.5

Sample size is calculated by sample size calculator (sample size determination in health studies, WHO). Pradeep et al. [18] reported that the mean gingival index score at 6 weeks interval in Metronidazole gel group was 1.43 ± 0.27 while the mean gingival index score in Metronidazole and Chlorhexidine combination gel was 1.01 ± 0.38.

Keeping the above difference at the level of significance (α) at 5% and power of study (1-β) at 95%, we need at least 22 observations. We inflated the number to get 30 subjects per group.

Since, we have three experimental groups, so we need a total of 90 subjects.

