#### Inclusion criteria

2.6.1

•Patients having 20 or more teeth•Systematically healthy patient with no co-morbids•Subjects with clinically confirmed gingivitis (bleeding on probing ≥10%)

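### The GEE sentence names only the correlation among sites of a tooth; if the tooth is the cluster, standard errors for site-level arm comparisons are too small

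*Protocol article*

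**What the plan says.** All of the following is in the protocol article.

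- **Analysis (Data analysis, section 3).** "Generalized estimation equation (GEE) will be run to account for the correlated data (six probing sites per tooth) for the comparison of study arms". The parenthesis is the only description of the correlation the model is meant to handle. The section names no subject or cluster variable, working correlation or outcome for the GEE. The test level is given as follows: "The level of significance will be kept at 0.05".
- **Unit of randomisation (section 2.10).** "Subjects will be assigned to one of the three study groups using a computer generated randomization list". The Sample size section (2.5) also counts in patients: 30 per group, 90 in all.
- **Unit of measurement (Procedure, section 2.9).** "The bleeding sites, probing depth and the gingival index score will be calculated for all the teeth (six sites per tooth". The Inclusion criteria (section 2.6.1) require "Patients having 20 or more teeth".
- **Outcomes.** The primary outcome (section 2.1.1) is bleeding on probing as a percentage, at two and six weeks. The Data analysis section assigns bleeding sites to a Friedman test.

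**The concern.** The gel is assigned to a person, and every tooth in that person's mouth shares the gel, the brushing habits and the host response. For a comparison of arms, the independent units are therefore patients. A robust GEE variance is valid only if the clusters are independent of one another.

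The article is not simply silent here. It states a level of correlation, and that level is the tooth. An analyst who follows the sentence literally would declare the tooth as the GEE subject. The variance would then allow for sites of one tooth being alike but not for teeth of one mouth being alike. Thirty patients per arm would enter as at least 30 × 20 = 600 independent units. Confidence intervals would be too narrow, and the test would reject a true null hypothesis more often than the stated 5%.

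**Working it through.** **1. The plan's own figure.** The Sample size section states "level of significance (α) at 5% and power of study (1-β) at 95%, we need at least 22 observations". Its inputs are "mean gingival index score at 6 weeks interval in Metronidazole gel group was 1.43 ± 0.27" and "mean gingival index score in Metronidazole and Chlorhexidine combination gel was 1.01 ± 0.38", so the difference is 1.43 − 1.01 = 0.42. Using n = 2(z₀.₉₇₅ + z₀.₉₅)² SD² / d² with the larger SD of 0.38:

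2 × (1.960 + 1.645)² × 0.38² / 0.42² = 21.3, rounded up to 22.

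The figure reproduces two-sided with that SD; the pooled SD of 0.330 would give 17. It is a count of patients. It does not settle what the GEE cluster is, but it shows that the trial was sized on patients.

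**2. Inputs for the clustering check.**
- Teeth per patient: m = 20, the minimum in the Inclusion criteria. As a sensitivity value, m = 28 is assumed.
- Nominal level: 0.05, taken as two-sided (the article does not say).
- ICC of tooth means within a patient, ρ: not in the article; assumed 0.01 to 0.30.

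**3. Formula.** Let a tooth mean have variance σ². The mean of m teeth in one patient has variance (σ²/m)[1 + (m − 1)ρ]. A variance clustered on tooth estimates only σ²/m. Correlation among the six sites is already inside σ², so the part left out is

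DEFF = 1 + (m − 1)ρ.

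The estimated standard error is 1/√DEFF of its correct size, and the true two-sided level is 2[1 − Φ(1.96/√DEFF)].

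**4. Results.**

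| Assumed ICC | DEFF, 20 teeth | SE relative to correct | True level, 20 teeth | True level, 28 teeth |
|---|---|---|---|---|
| 0.01 | 1 + 19 × 0.01 = 1.19 | 0.92 | 0.072 | 0.082 |
| 0.05 | 1.95 | 0.72 | 0.160 | 0.201 |
| 0.10 | 2.90 | 0.59 | 0.250 | 0.308 |
| 0.30 | 6.70 | 0.39 | 0.449 | 0.516 |

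**5. Check by simulation.** Binary bleeding sites were generated under the null with two arms of 30 patients, 24 teeth, six sites per tooth and 40% bleeding, with 2,000 runs per setting. Robust standard errors were clustered first on tooth, then on patient.

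| ICC of tooth means | Rejection, tooth cluster | Formula, m = 24 | Rejection, patient cluster |
|---|---|---|---|
| 0 (no patient effect) | 0.051 | 0.050 | 0.058 |
| 0.077 | 0.247 | 0.239 | 0.060 |
| 0.198 | 0.391 | 0.406 | 0.051 |
| 0.314 | 0.507 | 0.494 | 0.071 |

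The formula and the simulation agree. Clustering on patient brings the level back to 0.051–0.071. The slight excess over 0.05 is consistent with an uncorrected robust variance on 30 clusters per arm. Tooth clustering is harmless only when teeth of one mouth are uncorrelated.

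**The case against.** The strongest reply is that the article never says the tooth is the cluster. The parenthesis echoes the measurement description in the Procedure section and may simply explain why GEE is needed, with the patient as subject. On that reading the robust standard errors are valid, and the sentence is only loosely worded. The subject variable and working correlation are also details that a condensed article commonly leaves to a fuller document. This stands in part: patient-as-subject is possible, and a reader who infers that the protocol has fixed the tooth as cluster goes beyond the text. But the sentence does commit itself to a level of correlation, and for a patient-randomised comparison that level is incomplete. This is more than silence.

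A second reply is that the primary outcome may be untouched. Bleeding as a percentage is naturally one value per patient, bleeding sites are assigned to the Friedman test, and the mention of probing sites may point to probing depth, a secondary outcome. This stands. A reader might infer that the primary result is compromised; the article does not support that, because it does not say which outcomes enter the GEE. Equally, it excludes none. The GEE is the method it names expressly for comparing the arms, and the Friedman test, being for related samples, cannot take over that task.

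A third reply concerns size. A reader might infer that the type I error will be several times 5%. No ICC is given, and at 0.01 the true level is only about 7%. The larger figures depend on the assumed ICC.

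**Conclusion.** The point holds conditionally. Read literally, the GEE sentence leaves out the correlation between teeth of one mouth. If the tooth is used as the cluster, standard errors for every site-level outcome in the GEE are understated whenever that correlation is positive. With 20 teeth per patient the true level at nominal 5% is about 7%, 16%, 25% and 45% for assumed ICCs of 0.01, 0.05, 0.10 and 0.30, and higher with more teeth.

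The direction rests on the design alone: patient-level assignment with many teeth per patient. The size rests on the assumed ICC, a two-sided test and equal numbers of teeth per patient. The conclusion does not extend to one whole-mouth value per patient, and it falls away if the patient is in fact the GEE subject.

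**What to change.** Rewrite the GEE sentence in the Data analysis section so that it names the patient as the GEE subject (cluster), with tooth, site and visit as levels within patient, and robust standard errors. State which outcomes are analysed this way, with a binomial model and logit link for site-level bleeding. The alternative is to reduce each outcome to one value per patient per visit, such as the whole-mouth bleeding percentage, and compare the arms on that.

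The cost is one sentence and one setting in SPSS, with no new data or patients. Compared with a tooth-clustered run, confidence intervals become wider, and correctly so. If the patient was always the intended subject, only the wording changes.

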### Null hypothesis

1.1

0.8% Metronidazole gel, 0.2% Chlorhexidine gel and combination of both Metronidazole and Chlorhexidine gels are equally effective in reducing gingival inflammation.

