#### Primary outcome measure

2.1.1

Bleeding index (BOP in percentage) [Two weeks and six weeks]

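### The Friedman test named for bleeding sites does not fit three independent arms, and the plan does not say whether the GEE is the primary analysis of BOP

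*Protocol article*

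**What the plan says.** All references are to the protocol article.

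- **Primary outcome measure (2.1.1):** "Bleeding index (BOP in percentage) [Two weeks and six weeks".
- **Null hypothesis (1.1):** the two single gels and the "combination of both Metronidazole and Chlorhexidine gels are equally effective in reducing gingival inflammation". This is a statement about differences between arms.
- **Randomization, blinding and treatment allocation (2.10):** "Subjects will be assigned to one of the three study groups using a computer generated randomization list". No crossover, split-mouth or matched design is described anywhere.
- **Procedure (2.9):** "The bleeding sites, probing depth and the gingival index score will be calculated for all the teeth (six sites per tooth".
- **Data analysis (3), first method:** "Generalized estimation equation (GEE) will be run to account for the correlated data (six probing sites per tooth) for the comparison of study arms". No outcome is named.
- **Data analysis (3), next sentence:** "Friedman test will be used to assess the bleeding sites among three study groups at the baseline and endpoint". This is the only sentence that ties a named test to bleeding.

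The section also adopts an intention-to-treat approach and a 0.05 significance level. It does not say which of the two methods is the primary analysis of BOP.

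**The concern.** The Friedman test is for related samples. It ranks the values within each block, normally one subject under several conditions, and compares rank sums across conditions. Here the three groups are different people, so no block contains one value from each arm.

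An analyst following the sentence literally would have to lay the arms side by side and let the row number create the blocks. The p-value would then depend on how the file is sorted. The arms would have to be the same size. A row with one missing value would be dropped together with two other patients' data, which sits badly with intention to treat.

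If the analyst instead uses visits as the conditions within each arm, the test is legitimate but says nothing about one gel against another.

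The analysis of the primary outcome is at stake. A reader cannot tell whether the trial's conclusion on BOP will come from an ill-fitting test or from the GEE, and the two can disagree.

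**Working it through.** **1. The two readings of the Friedman sentence.**

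| Reading | Blocks | Conditions | What it tests |
|---|---|---|---|
| Between arms (the literal wording) | File rows, i.e. unrelated patients | Arms A, B, C | Arm difference, with arbitrary blocking |
| Within each arm | Patients | Visits | Change over time; no arm comparison |

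Neither is a sound test of the null hypothesis in 1.1. On the second reading, baseline and endpoint also supply only two time points.

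**2. An effect size to work with.** The documents give no planning effect for BOP. The only one is for the gingival index at 6 weeks (Sample size, 2.5): "Metronidazole gel group was 1.43 ± 0.27" and "Metronidazole and Chlorhexidine combination gel was 1.01 ± 0.38".

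- Difference: 1.43 − 1.01 = 0.42.
- With the larger SD: 0.42 / 0.38 = 1.1 SD.
- With the pooled SD, √[(0.27² + 0.38²)/2] = 0.3296: 0.42 / 0.3296 = 1.27 SD.

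The plan's own figure reproduces from these inputs. With SD 0.38 in both arms, two-sided 5% and 95% power, n = 2(1.960 + 1.645)² × 0.38² / 0.42² = 21.3, i.e. 22 per group, which the plan raises to 30. The sample size is not affected by this point.

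**3. Simulation of the between-arm reading.** Assumptions: 30 per arm, normal data, one arm shifted, nominal 5% level, Friedman applied to arbitrarily matched rows. A dataset counts as dependent on row order if between 5% and 95% of 100 random sorts gave p < 0.05. The figures are rounded over repeated runs.

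| Shift | Friedman power | Kruskal-Wallis power | Significance depends on row order |
|---|---|---|---|
| 0.7 SD (assumed; no source in the documents) | about 66% | about 77% | roughly 60–75% of datasets |
| 1.1 SD (gingival index, larger SD) | about 97% | about 99% | about 12–15% |
| 1.27 SD (gingival index, pooled SD) | about 99% | over 99% | about 3–4% |

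At smaller assumed shifts the power figures are 39% v 47% (0.5 SD) and 52% v 63% (0.6 SD).

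**4. Type I error.** With no difference between arms, Friedman rejected in about 5.5–6.2% of trials and Kruskal-Wallis in about 5%. Random row matching wastes information but does not materially inflate false positives.

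**5. One dataset, re-sorted.** In a single simulated dataset with a true shift of 0.6 SD, 5,000 re-orderings of patients within arms moved the Friedman p-value between 0.0003 and 0.97 (central 95% range 0.02 to 0.65). About 15% of orderings fell below 0.05. Kruskal-Wallis, which ignores order, gave 0.11 throughout. With unequal arms (30, 29 and 28) the Friedman test could not be computed.

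**6. The GEE.** Its sentence refers to six probing sites per tooth, and Procedure (2.9) records bleeding at six sites per tooth. Bleeding therefore falls within the data that the GEE describes. But the next sentence gives bleeding sites a separate test, and nothing ranks the two.

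**The case against.** The strongest reply is that the plan already holds a suitable kind of between-arm method. The GEE is planned expressly to compare study arms on site-level data, and bleeding is recorded at those sites. Friedman, as a repeated-measures test mentioned alongside baseline and endpoint, may have been meant only as a time trend within each group. On that view it is supplementary and not invalid.

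Much of this stands. A reader might infer that the primary question goes unanswered as planned; the documents do not support that, because the GEE could answer it. A reader might also infer that the trial will draw its conclusions from separate within-arm p-values. Nothing in the Data analysis section says so, and it does plan a comparison of arms. Nor is there support for a claim of serious false-positive inflation.

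It is also fair that a 0.7 SD shift has no source in the documents and that the loss is small at the effect used for the sample size. That effect is for the gingival index, however, so it is only a guide for BOP. The intention-to-treat conflict arises only on the row-matched reading, and only with missing values or unequal arms.

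What does not stand is that the GEE settles the matter. Its sentence names no outcome, the following sentence assigns bleeding to Friedman, and the wording there is across the three groups, not across visits. This is also not a detail left open for a separate analysis plan: the article names a specific test, and that test does not fit the design.

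**Conclusion.** The point holds in this form: the only test tied by name to the primary outcome is unsuited to comparing three independent arms, and the plan does not say whether the GEE, which could do so, is the primary analysis of BOP.

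If Friedman were used between arms, the cost would be arbitrariness and lost power. About 11 percentage points of power would go at an assumed 0.7 SD (66% v 77%), but only about 2 points at 1.1 SD and less at 1.27 SD. Dependence on row order follows the same gradient. These figures rest on normal data, 30 complete patients per arm and a shift in one arm only; the true effect and distribution for BOP % are not given.

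The baseline comparison of arms in the same sentence is uninformative after randomisation, but it does not bias the primary result.

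**What to change.** Replace the Friedman sentence with one named primary between-arm analysis of BOP at a stated visit. Either of these would do:

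- the GEE already planned, applied to site-level bleeding, with arm as a factor and clustering on patient; or
- a patient-level model of BOP % with arm as a factor, or Kruskal-Wallis across the three arms at follow-up if a rank test is preferred.

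Whichever is chosen, state that it is primary. If the other is kept, label it as supportive. Retain Friedman at most as a descriptive within-arm time trend across the three visits, and drop the significance test of arms at baseline, leaving the baseline descriptive statistics.

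The cost is one sentence in the Data analysis section. Sample size, visits and patient procedures do not change. The choice should be fixed before unblinding.

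### No baseline covariate is named for any arm comparison, and the Friedman test assigned to bleeding cannot take one; adjusting for baseline would be a free gain in precision

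*Protocol article*

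**What the plan says.** The primary outcome is bleeding on probing as a percentage, at two and six weeks. Gingival index, oral hygiene index and probing depth are secondary at the same times (Primary and Secondary outcome measures).

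Baseline data exist. For the first visit, Procedure states: "The bleeding sites, probing depth and the gingival index score will be calculated for all the teeth (six sites per tooth"). Data analysis also lists oral hygiene index among the baseline parameters to be summarised.

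The Data analysis section then names three things:

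- a GEE to compare the arms while allowing for correlated probing sites, with no outcome, visit term or covariate given;
- a Friedman test to "assess the bleeding sites among three study groups at the baseline and endpoint";
- for the two indices: "Similarly, gingival index and oral hygiene index in the three groups at baseline, after 2 weeks and 6 weeks will be compared".

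Baseline appears as something to summarise and as a time point to compare. It is nowhere named as a covariate.

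**The concern.** When the same measure is taken before and after treatment, part of the spread at follow-up is variation between patients that was already visible at baseline. A model with the baseline value as covariate removes that part from the error. It also allows for chance differences between arms at baseline; with 30 per arm, the SD of such a difference between two arms is √(2/30) = 0.26 SD.

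The one test named for the primary outcome has no covariate term, so no further detail elsewhere could add baseline adjustment to it. If it contrasts visits within an arm, it does not compare arms. If it is meant to contrast arms at baseline, it tests a null hypothesis that randomisation already makes true. On neither reading does baseline sharpen the treatment comparison. What is at stake is the width of the intervals and the power to separate three active arms.

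**Working it through.** **Inputs from Sample size.** Metronidazole: "mean gingival index score at 6 weeks interval in Metronidazole gel group was 1.43 ± 0.27". Combination: "mean gingival index score in Metronidazole and Chlorhexidine combination gel was 1.01 ± 0.38". Difference: 1.43 − 1.01 = 0.42. Alpha is 0.05 and power 0.95. Stated requirement: "we need at least 22 observations", read here as per group, then inflated to 30 per group.

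**Step 1: reproduce the plan's figure.** With the larger SD of 0.38, two-sided, normal approximation:

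n = 2 × (1.960 + 1.645)² × 0.38² / 0.42² = 21.3, rounded up to 22. This matches. A pooled SD of √((0.27² + 0.38²)/2) = 0.330 would give 17, so 0.38 is kept below.

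**Step 2: power at 30 per arm without adjustment.** The standard error of a difference is 0.38 × √(2/30) = 0.0981.

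- At 0.42: 0.42/0.0981 − 1.960 = 2.32, so power is 99.0%.
- At 0.21, half the planned difference and chosen only for illustration: 0.21/0.0981 − 1.960 = 0.18, so power is 57%.

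**Step 3: effect of adjustment.** In a linear model with one value per patient, adjusting for baseline multiplies the residual variance by 1 − ρ², where ρ is the within-arm correlation between baseline and follow-up. The documents give no ρ, so it is an assumption shown over a range. The standard error is multiplied by √(1 − ρ²), and 30 per arm is worth 30/(1 − ρ²) unadjusted patients. The difference detectable at 80% power is (1.960 + 0.842) × 0.0981 × √(1 − ρ²).

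| Assumed ρ | 1 − ρ² | SE ratio | 30 per arm is worth | n replacing 22 | Detectable at 80% power | Power at 0.42 | Power at 0.21 |
|---|---|---|---|---|---|---|---|
| 0 (unadjusted) | 1.00 | 1.000 | 30.0 | 22 | 0.275 | 99.0% | 57% |
| 0.2 | 0.96 | 0.980 | 31.2 | 21 | 0.269 | 99.2% | 59% |
| 0.3 | 0.91 | 0.954 | 33.0 | 20 | 0.262 | 99.4% | 61% |
| 0.5 | 0.75 | 0.866 | 40.0 | 16 | 0.238 | 99.9% | 70% |
| 0.7 | 0.51 | 0.714 | 58.8 | 11 | 0.196 | >99.9% | 85% |

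**Step 4: in SD units.** The difference detectable at 95% power with 30 per arm is 3.605 × √(2/30) = 0.93 SD unadjusted, and 0.89, 0.81 and 0.66 SD at ρ = 0.3, 0.5 and 0.7. The planned gingival index difference is 0.42/0.38 = 1.11 SD.

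**Step 5: bleeding.** The article gives no SD or target difference for the primary outcome, so the gain cannot be expressed in percentage points of bleeding.

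**The case against.** Several stronger readings are tempting, and the documents do not support them.

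*The plan rules out baseline adjustment.* It does not say so. A GEE is named for the arm comparison, its terms are not given, and a condensed article may leave them to a fuller document. This stands as a limit on the claim. The stated Friedman test for bleeding is not an omission, however, and it cannot be adjusted.

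*The plan tests the arms against each other at baseline.* That is one reading. Friedman is a related-samples test, so the sentences may describe change over visits within each group, and the section also lists baseline values under descriptive statistics. The wording does not settle it.

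*The trial is too small without adjustment, or its comparisons are biased.* Neither follows. On the plan's own gingival index inputs, 30 per arm gives about 99% power. An unadjusted comparison of randomised arms is valid, and chance imbalance is already part of its standard error. That power figure, though, concerns a secondary outcome and one pair of arms. It says nothing about bleeding or the contrasts with chlorhexidine alone.

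*The gain is large.* The correlation is unknown and may be low. Entry requires bleeding on probing of at least 10%, which cuts off the lower end of baseline values, and all arms have scaling and polishing between the two-week examination and the six-week visit. At ρ = 0.3 the standard error falls by only about 5%. The factor 1 − ρ² also belongs to a linear patient-level model and does not carry over directly to a GEE on site-level bleeding.

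**Conclusion.** The point holds as a loss of efficiency, not as a bias or an error of validity. The stated analysis names no baseline covariate, and the test given to the primary outcome cannot use one, although the values are collected. Over the assumed correlations of 0.3 to 0.7 the residual variance would fall by 9% to 49%. At the planned gingival index difference this changes little. At half that difference, power would rise from 57% to between 61% and 85%. For bleeding, precision is undocumented, so neither the need nor the gain can be sized. These figures rest on an assumed correlation, an SD of 0.38, a two-sided 5% level, the normal approximation and one value per patient per visit. This is a free improvement.

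**What to change.** In section 3, Data analysis:

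- Replace the Friedman test as the between-arm analysis of bleeding with the GEE already planned. Take the patient as cluster; arm, visit (2 and 6 weeks) and arm-by-visit as terms; and the patient's baseline value of the same measure as covariate. Report the arm contrasts at each visit.
- Use the same model for gingival index, oral hygiene index and probing depth.
- State that baseline values are described by arm and not tested between arms.

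The cost is a rewritten paragraph and one model parameter per outcome. No patients or visits are added. One check is needed: Procedure does not list oral hygiene index among the first-visit measurements although Data analysis counts it as a baseline parameter, so the study proforma should be confirmed to record it. The statistician is to be blinded to the groups, so the change can be fixed in writing before the codes are released.
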